### RCT study design

This trial evaluates the effectiveness of an Enhanced Care intervention (opt-out) versus Standard Care (opt-in) in promoting tobacco cessation among retired FDNY-WTCHP responders who are eligible for LDCT lung cancer screening based on their self-reported smoking history. Using a parallel-arm design, the trial compares these interventions among WTC-exposed responders who currently smoke (Fig. 2). The Enhanced Care intervention includes opt-out enrollment in tobacco treatment, in which participants receive services unless they actively decline, tailored counseling with biofeedback based on LDCT scan and spirometry results, and varenicline with preloading, initiated before the target quit date, along with NRT as needed. In contrast, the Standard Care intervention requires opt-in enrollment and offers standard counseling without personalized biofeedback, and varenicline with preloading, initiated before the target quit date.

All participants follow a standardized treatment protocol that includes varenicline preloading for four weeks prior to the target quit date, followed by 12 weeks of varenicline. Counseling sessions are conducted via telehealth at baseline and weeks 2, 4, 8, 12, and 16, with a final follow-up at week 28. Research assessments are completed online at the same time points: baseline and weeks 2, 4, 8, 12, 16, and 28. Nicotine metabolite urine testing is conducted at Quest Diagnostics labs near participants’ homes. Participants receive a $30 gift card for each research visit they complete, which includes a complete questionnaire, a counselor visit, and a urine test. These measures are designed to enhance participation, adherence, and consistency across both intervention groups, supporting a thorough evaluation of factors influencing cessation outcomes.

The primary objectives of the trial are to compare enrollment rates between the Enhanced Care and Standard Care groups (objective 1), to analyze the impact of sociodemographic and clinical factors on enrollment, and to assess program outcomes: retention, adherence to varenicline and counseling, and tobacco abstinence (objective 2). A summary of study activities is described in Table 2.

**Table 2 Tab2:** Patient timeline by treatment arm: Enhanced Care and Standard Care

	Enrollment		Baseline (Week 0)		Week 2		Week 4		Week 8		Week 12		Week 16		Week 28	
	S	E	S	E	S	E	S	E	S	E	S	E	S	E	S	E
Enrollment																
**Randomization**: Randomization to treatment group	X	X														
**Opt-out enrollment with counseling**: Participants receive a letter outlining *opt-out* enrollment in the free FDNY-WTCHP Tobacco Cessation Program for CT. Those who do not opt out are proactively contacted by the Research Coordinator to discuss treatment options, explain study procedures, and obtain informed consent. Participants who indicate they do not wish to participate are excluded from the study and are not contacted again, ensuring respect for their preferences.		X														
**Opt-in enrollment with counseling**: Participants are invited to *opt into* the free FDNY-WTCHP Tobacco Cessation Program through a letter describing the program and its benefits, including personalized counseling and support. Enrollment requires the participant to initiate contact, expressing interest in tobacco treatment. The program provides counseling sessions tailored to help participants quit smoking and improve their overall health.	X															
**Treatment visits**																
**Enhanced Counseling**: Telehealth counseling by certified tobacco treatment specialists, focusing on skills per Public Health Service guidelines, personalized biofeedback on LDCT/spirometry results, varenicline support, and lung cancer risk reduction to leverage or enhance motivation.				X		X		X		X		X		X		X
**Standard Counseling**: Certified tobacco treatment specialists provide brief telehealth counseling focused on skill-building in accordance with Public Health Service guidelines, along with varenicline support. Sessions do not include discussions of LDCT/spirometry results.			X		X		X		X		X		X		X	
**Varenicline dosing**: Both groups: 0.5 mg once daily for 3 days, 0.5 mg twice daily for 4 days, then 1 mg twice daily from day 8 onward.			X*	X*	X*	X*	X	X	X	X	X	X	End of treatment			
**Self-administered questionnaires: Both groups -** Patients complete web-based questionnaires			X	X	X	X	X	X	X	X	X	X	X	X	X	X
**Urine collection**																
Both groups - Urine samples will be collected at Quest Diagnostics to measure nicotine metabolite levels			X	X	X	X	X	X	X	X	X	X	X	X	X	X

**E = Enhanced Care S = Standard** Care* Varenicline preloading: Varenicline initiated four weeks prior to target quit date (TQD) followed by 12 weeks of varenicline post-TQD, for a total of 16 weeks of treatment, to reduce pre-treatment smoking enjoyment and increase tobacco abstinence

**Fig. 2 Fig2:**
[figure not shown]
Flow of Participants Through Recruitment, Enrollment, and Study Procedures. **Legend**: This figure illustrates the participant flow for a randomized trial comparing Enhanced Care and Standard Care smoking treatment programs among WTC-exposed responders who smoke. Recruitment strategies differed between groups, with Enhanced Care participants receiving an “opt-out” invitation and Standard Care participants required to “opt-in.” The flowchart outlines the stages of recruitment, enrollment, and study procedures, including eligibility screening, exclusion criteria, counseling sessions, varenicline treatment, and telehealth-based follow-ups. Key study activities, such as research assessments and participant compensation, are also detailed

### Surveys

Baseline and follow-up surveys, conducted within three days of each counseling visit, include comprehensive assessments to monitor smoking behaviors and ensure the continued appropriateness of varenicline use. Baseline surveys cover smoking history, current tobacco use, alternative tobacco use [32, 33], nicotine dependence (via the Fagerstrom Test for Nicotine Dependence) [8], prior quit attempts [34], and cessation motivation [35, 36] and self-efficacy.^36^ Tobacco-related questions include a past-month timeline follow-back (TLFB) calendar [37–40] to capture detailed smoking patterns and daily cigarette consumption. Emotional and psychological domains are assessed using the SF-12 for quality of life [41], the Center for Epidemiologic Studies-Depression (CES-D) scale for depressive symptoms [42, 43], and the Post-traumatic Stress Disorder Checklist (PCL-17) for trauma-related symptoms [44, 45]. Alcohol use is screened using the Alcohol Use Disorders Identification Test (AUDIT) [46], and the Columbia-Suicide Severity Rating Scale (C-SSRS) identifies suicidal ideation or behaviors, triggering immediate intervention when necessary [47]. In cases of a positive C-SSRS screen, the director of mental health services at FDNY is immediately notified via automated text message and email to ensure timely follow-up and support. Follow-up surveys (weeks 2, 4, 8, 12, 16, and 28) focus on tobacco-related questions, including the TLFB calendar and the C-SSRS, to monitor smoking behaviors and ensure participant safety while reducing survey burden. All surveys are completed at home electronically on FDNY-WTCHP’s cloud-based platform. If participants encounter difficulties with technology, surveys will be conducted by a study coordinator by phone to ensure data collection continuity and minimize participant burden.

### Counseling approach

All participants receive seven structured telehealth counseling sessions (via Microsoft Teams) with a certified tobacco treatment specialist. These sessions focus on evidence-based strategies, including problem-solving, skills training, and biofeedback, ensuring fidelity and consistency across study arms while addressing individual needs. Counseling sessions also reinforce adherence to the varenicline regimen (S1).

The counseling approach is informed by a comprehensive checklist adapted from The Manual of Smoking Cessation: A Guide for Counsellors and Practitioners (S2) [48]. Key components include assessing withdrawal symptoms, facilitating action planning, addressing lapse triggers, and reinforcing an identity as someone who has quit smoking. Education on nicotine monitoring and pharmacological aids, combined with biofeedback, ensures participants receive consistent, evidence-based support.

Counseling sessions include building rapport, assessing smoking behaviors and readiness to quit, addressing withdrawal symptoms, and managing barriers to cessation. Participants receive tailored advice on avoiding social smoking cues, restructuring their environment, and developing coping strategies to prevent relapse. Behavioral action plans, goal setting, and progress reviews are integral to each session. Education on the health benefits of quitting, the purpose of nicotine monitoring, and the use of pharmacological aids are also provided. Participants are encouraged to self-record tobacco use, identify reasons for quitting, and engage with social support systems.

Participant’s contact information is verified and updated before each counseling visit. The research team maintains regular communication with participants to optimize retention. These include text messages, e-mail and phone call appointment reminders. Telehealth counseling visits accommodate participant preferences and ensure consistency. Missed visits are rescheduled twice: first on the same day the session was missed and again one week later if the participant has not responded. If the visit is not completed before the next scheduled research visit, it is recorded as missed. Refused sessions are not rescheduled, but counseling is re-offered at the next research visit. Counseling sessions follow the same schedule as research visits, with their timing based on the date of the baseline visit. Missed content may be addressed in a later session or replaced with the scheduled material, as determined by the tobacco treatment specialist.

### Enhanced Care arm

In the Enhanced Care arm, counseling integrates biofeedback from participants’ LDCT and spirometry results to create periods of increased health awareness that may enhance receptivity to behavior change [5, 49]. For individuals with LDCT abnormalities (e.g., nodules, bronchial wall thickening, emphysema, chronic obstructive pulmonary disease (COPD), or fibrosis), counseling highlights the benefits of smoking cessation, including the potential resolution of inflammation in ground-glass nodules and a slower progression of disease. Spirometry results indicating accelerated lung function decline or dysfunction are used to highlight the benefits of quitting in slowing disease progression. Participants with normal findings are counseled on long-term health benefits and preventing future complications. Nicotine metabolite results are incorporated to provide additional biofeedback, reinforcing adherence to the treatment program and titrating nicotine replacement medications when necessary. Nicotine replacement medications are added, if necessary, to attenuate break-through withdrawal symptoms and/or to attain complete abstinence. Enhanced Care sessions are structured to last between 30 and 40 min.

### Standard Care arm

In the Standard Care arm, counseling follows the same structured framework but does not incorporate tailored biofeedback from LDCT or spirometry results. Participants in this arm receive varenicline including preloading. Instead, the sessions focus on general strategies for quitting smoking and maintaining abstinence. Standard care sessions are designed to be brief, typically lasting under 15 min.

### Consistency and fidelity

All counseling sessions are delivered by the same certified tobacco treatment specialist to ensure consistent delivery and minimize differential bias between study arms. To maintain protocol adherence, the tobacco counselor uses a Fidelity Checklist during sessions (S1). This checklist ensures that key components, such as assessing smoking behavior, reviewing medication use, and addressing barriers, are consistently addressed. For Enhanced Care participants, the checklist ensures tailored discussions of LDCT, spirometry, and nicotine metabolite results occur when appropriate. The duration of each session is documented. To maintain impartiality and minimize social desirability bias, the counselor does not perform outcome assessments.

### Pharmacological support

All participants, regardless of study arm, receive a total of 16 weeks of varenicline: preloading for four weeks prior to the participant’s target quit date, followed by 12 weeks of varenicline. Dosing is standard: 0.5 mg daily for three days, followed by 0.5 mg twice daily for days 4 through 7, followed by 1 mg twice daily thereafter. Varenicline preloading is offered to all participants to reduce pre-quit tobacco enjoyment and withdrawal symptoms. Varenicline preloading prior to the target quit date has been shown to reduce the rewarding effects of smoking and increase quit success rates [29]. In both the enhanced and standard care arms, appropriate NRTs are added to varenicline when necessary and substituted in cases of adverse drug events (ADEs) to ensure individual tolerability and safety. Nicotine replacement medications are added, when necessary, to attenuate break-through tobacco withdrawal symptoms and/or to attain complete abstinence.

### Assessment of eligibility and symptom monitoring

Participants are screened at screening and each subsequent research visit for serious or unstable conditions, including psychiatric hospitalization, decompensated cirrhosis, cardiovascular disease, seizure disorder, suicidal ideation or attempts, and adverse reactions to varenicline (S4). Withdrawal symptom severity is assessed using a 0–10 scale for symptoms such as craving, irritability, insomnia, nausea, headaches, and depression. These measures were used to ensure safety and monitor withdrawal effects during the study (S5).

### Measures

For Objective 1, which examines factors related to program enrollment, the primary outcome is FDNY Tobacco Cessation Program enrollment (Yes/No), comparing enrollment rates between Enhanced and Standard Care. Sociodemographic factors (sex, age, race, and occupation (firefighter versus EMS)) and clinical factors (LDCT results, spirometry, PTSD, depression, quality of life, prior quit attempts, and nicotine dependence) are measured as potential influences on program enrollment. Additionally, prior program participation and documented quit attempts in health records are recorded.

For Objective 2, which evaluates tobacco abstinence and participant retention across study arms, the primary outcome is biochemically confirmed 7-day point prevalence abstinence, assessed at both the end of treatment and the conclusion of follow-up. Participants receive requisition forms for urine testing at Quest Diagnostics, to be completed within three days prior to appointments. These tests, pre-paid through the FDNY-WTCHP, provide results to the tobacco counselor in the Enhanced Care arm before sessions. The research team assists participants in locating the nearest Quest Diagnostics facility and scheduling appointments as needed. Biomarkers assessed at baseline and prior to each counseling visit include anabasine, nicotine, and its metabolites (cotinine, 3’-hydroxycotinine, and nornicotine) to monitor smoking status and adherence. Cotinine is used to identify tobacco exposure (cutpoint: 20 ng/mL), while anabasine distinguishes active tobacco use from NRT (cutpoint: 2 ng/mL) [50].

### Analyses

For Objective 1, we will examine factors associated with program enrollment, including sociodemographic and clinical characteristics. Prior program participation and documented quit attempts will be analyzed to assess their influence on cessation program enrollment.

For Objective 2, factors associated with abstinence will be explored, including retention, adherence to counseling sessions, and adherence to varenicline. Pill counts at each visit will assess adherence to prescribed medication (S3). Appointment duration will be recorded as a measure of engagement and intervention adherence. Exploratory analyses will assess the impact of adherence on abstinence rates and examine the influence of Enhanced Care on motivation to quit and abstinence rates.

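### Retention is to be explored as a factor for abstinence, but a participant lost by the assessment has no urine result, so that association is either built in or not estimable

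*Protocol article*

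**What the plan says.** In the protocol article, the Analyses section states for Objective 2 that "factors associated with abstinence will be explored, including retention, adherence to counseling sessions, and adherence to varenicline", and adds: "Exploratory analyses will assess the impact of adherence on abstinence rates". The Methods paragraph of the abstract repeats the plan, with retention and adherence among the factors.

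The outcome is set in Measures: "the primary outcome is biochemically confirmed 7-day point prevalence abstinence, assessed at both the end of treatment and the conclusion of follow-up". By the schedule under RCT study design, these two times are week 16 and week 28. Verification is by laboratory urine test: "Participants receive requisition forms for urine testing at Quest Diagnostics, to be completed within three days prior to appointments".

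Counseling has seven sessions, at baseline and weeks 2, 4, 8, 12, 16 and 28. On timing, the Counseling approach section says: "Counseling sessions follow the same schedule as research visits, with their timing based on the date of the baseline visit". Payment covers the components together: "Participants receive a $30 gift card for each research visit they complete, which includes a complete questionnaire, a counselor visit, and a urine test". Varenicline adherence is assessed by pill count at each visit. Treatment runs for 16 weeks, with the target quit date after the first four.

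Retention also has a second role. RCT study design lists it with adherence and abstinence among the program outcomes, and Measures has Objective 2 evaluate it across the arms.

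**The concern.** The proposed explanatory variables and the outcome draw on the same follow-up. Someone who has left the study by week 16 or 28 has no urine result, so retention partly decides whether abstinence can be confirmed at all. If adherence is counted over the whole schedule, the count also includes sessions at or after the outcome, and tablets taken or not taken after a possible relapse.

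The risk lies in interpretation. A finding that retained and adherent participants quit more often could be reported as evidence that retention or attendance drives quitting, when the classification of missing results produced some or all of it. The word impact invites that reading. A program might then invest in retention on the strength of an artefact.

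**Working it through.** The article gives no sample size, retention rate or abstinence rate, so there is no figure to reproduce. The rates below are assumptions, chosen so that abstinence has **no** true relation to retention or attendance.

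**1. Order of events (from the article).**
- For week-16 abstinence, five sessions come before the outcome (weeks 0, 2, 4, 8, 12). The week-16 session normally follows the urine sample, which is due in the three days before the appointment. The week-28 session comes 12 weeks later.
- For week-28 abstinence, six sessions come before. The seventh normally follows the sample.
- Tablets run from week 0 to week 16 with the quit date at week 4, so 16 − 4 = 12 weeks of pill counts fall where relapse can already have occurred before the week-16 outcome. All tablet-taking precedes the week-28 outcome, by 28 − 16 = 12 weeks.

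**2. Retention at the outcome assessment.** Let p be true abstinence and r retention, independent of each other.
- *Missing = smoking:* confirmed abstinence is p in the retained and 0 in the non-retained; overall it is p × r. With p = 0.25 and r = 0.70, this is 25% against 0%, and 0.25 × 0.70 = 17.5% overall. For p from 15% to 35% the difference is always p itself.
- *Observed results only:* everyone analysed is retained. The factor has one level and no association can be estimated.
- *Imputation:* outcomes of the non-retained come from the imputation model, so the association is whatever that model assumes.

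Share of simulated trials (2,000 each) in which Fisher's exact test, two-sided 0.05, is significant under missing = smoking, with p = 25% and no true relation:

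| Participants | r = 60% | r = 70% | r = 80% |
|---|---|---|---|
| 50 | 68% | 53% | 20% |
| 100 | 99% | 99% | 86% |
| 200 | 100% | 100% | 100% |

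**3. Counseling attendance.** Assumptions: 25% true abstinence; mean attendance 70% over seven visits, varying between persons (beta distribution, concentration 2); outcome at the seventh visit. High attendance means at least 6 of 7 sessions or, when the outcome visit is left out, at least 5 of 6. The link is the share of participants whose outcome collection follows their attendance. For the rest it is independent.

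| Link | Missing = smoking, all 7 sessions: high vs low | Odds ratio | Odds ratio, earlier 6 sessions only |
|---|---|---|---|
| Full | 23.7% vs 11.3% | 2.45 | 2.03 |
| Half | 20.6% vs 14.4% | 1.54 | 1.41 |
| None | 17.4% vs 17.5% | 1.00 | 1.00 |

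First row from the rounded rates: (0.237/0.763) / (0.113/0.887) = 2.44; 2.45 unrounded. Among participants with an observed outcome the odds ratio is 1.00 in every row, with either session count.

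So leaving out the outcome-visit session reduces the artefact under missing = smoking but does not remove it. Restricting to observed outcomes removes it here. Dropout caused by relapse was not simulated; it would be a further source of bias.

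**The case against.** The strongest reply is that a condensed article need not define retention, the adherence window or the missing-outcome rule, and that a fuller document may do so. That holds for counseling and tablets, where the size of any artefact depends on those rules. It does not clear retention at the outcome assessment, which fails under either usual rule for missing urine. A definition taken from earlier visits would be needed, and the listed analysis does not state one.

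Three stronger readings are tempting and are not supported:
- *That abstinence can be confirmed only at an attended counseling session.* Urine is given at an outside laboratory before the appointment, surveys are completed at home with a telephone fallback, and refusing a session does not end research visits. The three-part visit is described as the condition for the gift card, not as a rule for observing the outcome. The shared schedule makes a link plausible, but the article does not fix its strength.
- *That participants moved to nicotine replacement after an adverse drug event are scored as non-adherent.* The article allows the substitution and says that pill counts assess adherence. It does not say how these participants are classified.
- *That all adherence measures overlap the outcome.* For week-28 abstinence, all varenicline exposure and six of the seven sessions come first.

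It is also fair to say that retention across arms is already planned, and that the association analyses are labelled as explored or exploratory.

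**Conclusion.** The point holds in a limited form. For retention, the planned association with confirmed abstinence is forced if missing counts as smoking (p against exactly 0%) and not estimable if only observed results are used. This needs no assumed rate, only that retention means being present at the outcome assessment. The false-positive shares do rest on assumed rates.

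For counseling adherence, the artefact is conditional: under missing = smoking the null odds ratio lies between 1.00 and 2.45 in the scenarios examined, depending on how closely outcome collection follows attendance. Sessions at weeks 16 and 28 are poor predictors in any case, because each normally follows the sample that defines the outcome. For varenicline, the concern is confined to the week-16 outcome, where low pill counts may partly be a consequence of relapse; no size can be given.

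The analysis is exploratory. The between-arm comparison of abstinence is unaffected, so this is a matter of wording and definition and does not threaten the trial's main result.

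**What to change.** Four changes to the Objective 2 analysis text, all on data already scheduled for collection:

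- Report retention as an outcome by arm and remove it from the factors for abstinence. If it is kept, define it only from visits before the outcome assessment in question.
- Count only the sessions and pill counts that precede each outcome assessment, for example through week 12 for week-16 abstinence.
- Show the associations among participants with an observed urine result alongside those with missing = smoking. The earlier cut-off alone is not enough, as the odds ratio of 2.03 shows.
- Replace impact with association.

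Costs: adherence after week 12 is not used as a predictor for week 16. The observed-outcome analysis can be selective if relapse drives dropout, which is why both versions should be shown. A pill count through week 12 still covers 12 − 4 = 8 weeks after the quit date, so it reduces the influence of relapse without removing it; a count over the four preloading weeks alone could be added as a sensitivity analysis.
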